## Methods

### Study design

The IMPROVE-it project will combine a cluster randomized controlled trial (cRCT) with a process evaluation to develop and study the in-depth effects of an intervention, a QIC, on contraceptive services and use. Harnessing QICs and co-design methods supported by National Quality Registers can ultimately help to close gaps between ordinary clinical practice and evidence-based guidelines [46, 48–51].

Figure 1shows the program theory of the project, which is based on a pilot study [47]. The project’s primary outcome is women´s choice of an effective contraceptive method within 16 weeks after giving birth. Effective contraception is defined as LARC (i.e. intrauterine devices and subdermal implants) and SARC (i.e. oral contraceptive pills, rings, patches, and injections).

### Study setting

In 2021, 30% of newborn children in Sweden had a mother who was born outside of Sweden [52]. The foreign-born population in Sweden is heterogenous, with some of the most common countries of birth for persons born outside of Europe being: Syria, Somalia, Iraq and Afghanistan [53]. In this study, refugees and asylum seekers are considered immigrants (foreign-born persons). Post-partum clinic visit(s), including contraceptive services available to all residents as part of public health services, should be offered within 16 weeks post-partum [54]. Midwives are the main providers of post-partum care and also administer the majority of contraceptive methods [55]. This cRCT will be conducted at 28 MHCs in the regions of Jonkoping, Vastra Gotaland and Stockholm. In 2021, these 28 MHCs had between 1900–3300 pregnant women yearly [56]. All MHCs in Jonkoping (22 MHCs, 3812 births) and Stockholm (94 MCHs, 26 191 births) were invited to participate. In Vastra Gotaland (94 MCHs, 17 595 births), we invited selected clinics of sufficient cluster size.

### Strategies used for recruitment

Managers at MHCs were contacted by co-authors EL or HK during 2019–2020 to inquire about their willingness to take part in the IMPROVE-it study. Due to the Covid-19 pandemic, the project’s commencement was postponed.

Initially, 29 MHCs accepted the invitation, finally 28 MHCs in three regions decided to participate. Informational meetings were held between the research team and the midwives at the MHCs during spring and fall 2021 before randomization was conducted.

### Eligibility of MHCs and inclusion criteria

Inclusion criteria: MHCs in the previously described regions with > 100 registered pregnant women during 2021 were invited to participate in the cRCT.

Intervention clinics commit to register women’s choice of contraception in the Swedish Pregnancy Register (SPR) during the post-partum MHC visit and participate in the QIC for 12 months [56]. The control clinics commit to provide routine care and register consenting women’s choice of contraception in the SPR.

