### Self-administered questionnaire

Inclusion criteria: Women 18 years and above coming for post-partum visits within 16 weeks post birth (live birth).

Exclusion criteria: Women who do not anticipate becoming sexually active with a male partner within six months.

Midwives at intervention and control clinics will invite women to participate in the study, i.e. respond to a digital or printed paper questionnaire during the visit and be contacted for follow-up six and 12 months post enrolment. There is also the possibility to participate in a telephone interview with an interpreter. Additional information will be provided at the MHCs before prospective participants give their written, digital or verbal informed consent.

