### The intervention – a QIC initiative

Midwives at the intervention clinics were invited to participate in the QIC initiative and gave their written consent to participate in the entire project. Midwives who joined the QIC after the first learning session (LS) were informed before participating in an LS. Through the consent process, participants agreed for LSs to be digitally recorded.

The intervention strategies presented at LSs will be applied at participating MHCs over nine months in 2022–2023 and follow those of the Breakthrough Series Collaborative model including [47]:- Four remote digitally run and recorded learning sessions (LS) every third month.- Action periods between every LS where participants apply learnings and evaluate changes in their MCH.- Co-design workshops with members of the target population.

The LSs will be informed by joint learning, self-reflection, co-design and evidence-based practice. At each LS, midwives in the intervention group will participate in competency-enhancing activities, exchange experiences about counselling as well as analyze and interpret data from the SPR regarding women’s choice of contraceptive methods. They will also decide on improvement activities that they would like to test in clinical practice during the action periods by using Plan Do Study Act (PDSA) cycles [58, 59]. Through the LSs, HCPs will also practice self-reflection, which has been described as an important factor in a previous study when seeking to facilitate co-design of health and related services [60]. Such sessions will also contribute to building trusting relationships between providers of various regions, a context factor found crucial to the implementation of successful continuing midwifery care [61].

Throughout the intervention, representatives from immigrant communities will be invited to co-design workshops with researchers to share their experiences of contraceptive services post-partum and provide feedback on midwives’ improvement activities, such as the development of visual aids for counselling. Personas will also be developed during these workshops to enable midwives to best understand and design services to meet the diverse needs of their patients [62].

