#### cRCT

The SPR will be used to retrieve the primary outcome, women’s choice of contraception, and covariates for evaluating social determinants such as age, sociodemographic characteristics and reproductive history. To evaluate secondary outcomes regarding participants’ satisfaction with the contraceptive counselling received, women attending the post-partum visit will complete a questionnaire that utilizes the Person-Centered Contraceptive Counseling Measure-scale (PCCC-scale) [65]. Participating women will also receive a follow-up questionnaire six and 12 months after the postpartum visit to evaluate their ongoing contraceptive use and satisfaction with the contraceptive method. In addition, the follow-up questionnaire will ask about unintended or planned pregnancy, induced abortion and miscarriages since the post-partum visit (Table 1).

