### Statistical analysis

The analysis population will consist of all women in the cRCT. Our primary goal is to estimate the effect of the QIC on choosing an effective contraceptive method using logistic regression analysis, relying on the randomization scheme to retrieve a causal estimate. We will also investigate whether the intervention effect varies by sociodemographic variables and reproductive history.

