## Discussion

Many health promotion and prevention studies have been carried out to improve SRHR services. Immigrants have collaborated on several health-related studies but have rarely been involved in all stages of the research process, especially the later implementation phases [42, 70]. Therefore, IMPROVE-it is designed to engage immigrants in the research process, especially in the intervention implementation phase, where representatives from immigrant communities will provide feedback on suggested improvement activities during co-design workshops.

The project will also bring forward women’s voices in that it will invite them to participate in a self-administered questionnaire regarding their choice of contraceptive method and satisfaction during CC at the post-partum visit. Importantly, to accommodate immigrant women’s views especially, we have translated the questionnaires into nine languages. Moreover, women who are illiterate will have the opportunity to participate and report their experiences via telephone with an interpreter. Data from the registers and potentially the self-administered questionnaire will be fed back to the midwives during the LSs as part of the QIC intervention.

Furthermore, the intervention includes co-design activities, including LSs created together with representatives from the target population that will use personas developed from focus group discussion data. This will enable HCPs to self-reflect and engage with immigrant women’s lived experiences of post-partum contraceptive services. Other co-design activities, such as workshops, will enable representatives from immigrant communities to provide feedback on suggested improvement activities regarding three evidence-based areas of change. To better understand the process of how the QIC is perceived, IMPROVE-it will evaluate organizational outcomes such as midwives’ confidence and competence. Ultimately, this intervention allows HCPs to have a direct impact on improving patient care by applying immediate changes to their practice that may be sustained over time.

However, a key limitation of the study is that it may be difficult to capture exactly how the intervention is delivered in the various health services regions and MHCs, since we have to rely on midwives self-reports of tested changes. To overcome this difficulty, we will triangulate our data by also collecting such information via coordinators and LS questionnaires.

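### The clinics' register commitment carries a consent condition in the control arm only, so the primary-outcome denominator needs one stated rule for both arms

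*Protocol article*

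**What the plan says.** Two adjacent sentences under *Eligibility of MHCs and inclusion criteria* set the clinics' commitments. For the intervention arm: "Intervention clinics commit to register women’s choice of contraception in the Swedish Pregnancy Register (SPR) during the post-partum MHC visit". Control clinics, besides giving routine care, are to "register consenting women’s choice of contraception in the SPR". The consent qualifier appears in the second sentence only.

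The register is the source of the primary outcome. Under *cRCT*: "The SPR will be used to retrieve the primary outcome, women’s choice of contraception, and covariates". Under *Statistical analysis*: "The analysis population will consist of all women in the cRCT".

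The only consent process described for women is under *Self-administered questionnaire*. It is the same in both arms and concerns the questionnaire and its follow-up: "Midwives at intervention and control clinics will invite women to participate in the study, i.e. respond to a digital or printed paper questionnaire". The Abstract describes the women in the trial as those who come to the routine post-partum visit in the first 16 weeks after birth, with no mention of consent or arm.

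**The concern.** Because the outcome exists only where a clinic has entered it, the registration commitment helps decide who has an outcome. If the two sentences are followed as written, intervention clinics enter women who attend and control clinics enter women who attend and consent.

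Clinics had been randomised before women were approached, so a woman's consent is a post-randomisation event. The analysis relies on randomisation for its causal reading. That reliance weakens if one arm is filtered by consent and the other is not. Women who agree to join a contraception study could differ from those who decline in contraceptive interest, language or migration background. If they do, the arms would differ even with no intervention effect, and the planned logistic regression would not in general remove the difference. An analysis plan also cannot recover outcomes that control clinics never entered.

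**Working it through.** **Step 1: what the text settles.** Setting the sections side by side:

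| Section | Intervention arm | Control arm |
|---|---|---|
| Eligibility of MHCs and inclusion criteria | registers women's choice, at the visit | registers consenting women's choice |
| Self-administered questionnaire | invitation and consent to questionnaire | same |
| cRCT | outcome from SPR | same |
| Statistical analysis | all women in the trial | same |

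Only the first row differs by arm, and none of the others overrides it. The last row leaves open whether consent is needed to be counted. No section says that the denominators differ, and none says that they are the same.

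**Step 2: size under the literal reading.** The plan gives no figure on this point. The benchmark is the 15-percentage-point increase under *Power analysis and randomisation*.

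Let p be the rate of effective-method choice among all attending women, the same in both arms (no intervention effect). Let c be the share of control women who consent, and d the rate in consenters minus the rate in non-consenters. Registration is taken as complete in the intervention arm, and complete among consenters in the control arm.

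- Intervention rate observed: p
- Control rate observed, consenters only: p + (1 − c) × d
- Apparent difference, intervention minus control: −(1 − c) × d

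The result does not depend on p. The documents give neither c nor d, so the values below are assumptions. Entries are percentage points.

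| c | d = −10 points | d = +10 points | d = +20 points |
|---|---|---|---|
| 0.5 | +5 | −5 | −10 |
| 0.7 | +3 | −3 | −6 |
| 0.9 | +1 | −1 | −2 |

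For example, c = 0.7 and d = +10 give −(1 − 0.7) × 10 = −3. If consenters choose effective methods more often, part of a true benefit is hidden. If they choose them less often, part of an apparent benefit is spurious. The difference is zero when d = 0 or c = 1.

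**Step 3: consent required in both arms.** With consent shares c_I (intervention) and c_C (control) and the same d, the apparent difference is (1 − c_I) × d − (1 − c_C) × d = (c_C − c_I) × d. Equal consent shares give zero. Unequal shares do not: c_I = 0.7, c_C = 0.5 and d = +10 give (0.5 − 0.7) × 10 = −2 points. A common consent rule removes the asymmetry in the text but not every selection risk.

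**The case against.** The strongest reply is that one adjective is being asked to carry too much. The sentences in question list what clinics commit to do; they do not define the analysis set. Everywhere the article describes the women, the outcome source or the analysis population, it makes no distinction by arm. Consent is sought in the same way in both arms and is tied to the questionnaire, not to register entry. Loose drafting in a condensed article is at least as plausible as a deliberate contrast of all attenders with consenters.

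This stands as a limit on what can be claimed. A reader might infer that control clinics enter only consenting women, that the denominators do differ, and that the comparison is biased. The documents state none of these.

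A reader might also infer that the learning sessions raise registration in the intervention arm, since midwives there will "analyze and interpret data from the SPR regarding women’s choice of contraceptive methods". That describes feedback on methods chosen, not on completeness. Both arms commit to register, and uneven completeness biases the result only if missing entries are related to the choice made. The documents do not establish this effect.

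The reply does not make the two sentences agree. The article states a rule and states it differently by arm. That is not a detail left to the analysis plan.

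**Conclusion.** The concern holds as an unresolved inconsistency in the rule that produces the primary outcome, not as a demonstrated bias. Under the text as written, inclusion would depend on post-randomisation consent in the control arm only, and the comparison would then be biased if consent is related to contraceptive choice.

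Neither size nor direction can be computed from the documents. The range of −10 to +5 points rests wholly on assumed consent shares of 0.5 to 0.9, assumed gaps of −10 to +20 points, and complete registration of the women each rule covers. It shows that the effect need not be trivial beside a 15-point target; it does not estimate it. If practice was uniform across arms, this asymmetry is absent and only the wording needs correcting.

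**What to change.** 1. State one SPR registration rule for both arms, preferably that the choice of every woman attending the post-partum visit within 16 weeks is entered, whether or not she consents to the questionnaire.
2. Define the analysis population as that same register denominator in both arms, and say explicitly that it does not depend on questionnaire consent.
3. Report SPR completeness by arm against the number of women attending, so that readers can see whether the rule was followed equally. If registration is already under way, state which rule each arm has followed.
4. If consent is legally required to use SPR data, apply the requirement in both arms, report consent rates by arm, and acknowledge the remaining selection risk shown in step 3 of the working.

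The Discussion describes a "self-administered questionnaire regarding their choice of contraceptive method and satisfaction during CC at the post-partum visit". An analysis of those answers can be at most supportive. It covers consenters only, and the questionnaire also excludes women who do not expect to be sexually active with a male partner within six months, so it cannot show what happened among women who declined.

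The cost is a short change to the protocol and clinic instructions, a count of attending women per clinic, and some added registration work at control clinics.

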### Self-administered questionnaire

Inclusion criteria: Women 18 years and above coming for post-partum visits within 16 weeks post birth (live birth).

Exclusion criteria: Women who do not anticipate becoming sexually active with a male partner within six months.

Midwives at intervention and control clinics will invite women to participate in the study, i.e. respond to a digital or printed paper questionnaire during the visit and be contacted for follow-up six and 12 months post enrolment. There is also the possibility to participate in a telephone interview with an interpreter. Additional information will be provided at the MHCs before prospective participants give their written, digital or verbal informed consent.

### Data management

A safe web application (REDCap) for builing and managing questionnaires will be used to secure data storage [57]. The web application allows the women who wish to participate to register personal data such as name, social security number, address, email address and mobile number via a QR code. These personal data will be pseudonymised, and the research subjects will receive a study ID. Paper questionnaires will be manually entered into the REDCap database. Three of the researchers (SB, [name] and AW) will promote data quality (e.g., prevent double data entry and conduct range checks for data values).

### The intervention – a QIC initiative

Midwives at the intervention clinics were invited to participate in the QIC initiative and gave their written consent to participate in the entire project. Midwives who joined the QIC after the first learning session (LS) were informed before participating in an LS. Through the consent process, participants agreed for LSs to be digitally recorded.

The intervention strategies presented at LSs will be applied at participating MHCs over nine months in 2022–2023 and follow those of the Breakthrough Series Collaborative model including [47]:- Four remote digitally run and recorded learning sessions (LS) every third month.- Action periods between every LS where participants apply learnings and evaluate changes in their MCH.- Co-design workshops with members of the target population.

The LSs will be informed by joint learning, self-reflection, co-design and evidence-based practice. At each LS, midwives in the intervention group will participate in competency-enhancing activities, exchange experiences about counselling as well as analyze and interpret data from the SPR regarding women’s choice of contraceptive methods. They will also decide on improvement activities that they would like to test in clinical practice during the action periods by using Plan Do Study Act (PDSA) cycles [58, 59]. Through the LSs, HCPs will also practice self-reflection, which has been described as an important factor in a previous study when seeking to facilitate co-design of health and related services [60]. Such sessions will also contribute to building trusting relationships between providers of various regions, a context factor found crucial to the implementation of successful continuing midwifery care [61].

Throughout the intervention, representatives from immigrant communities will be invited to co-design workshops with researchers to share their experiences of contraceptive services post-partum and provide feedback on midwives’ improvement activities, such as the development of visual aids for counselling. Personas will also be developed during these workshops to enable midwives to best understand and design services to meet the diverse needs of their patients [62].

### Defining outcomes and data collection methods

Reporting of the IMPROVE-it study results will follow the Standard Protocol Items for Clinical Trials (SPIRIT) [63, 64].

#### cRCT

The SPR will be used to retrieve the primary outcome, women’s choice of contraception, and covariates for evaluating social determinants such as age, sociodemographic characteristics and reproductive history. To evaluate secondary outcomes regarding participants’ satisfaction with the contraceptive counselling received, women attending the post-partum visit will complete a questionnaire that utilizes the Person-Centered Contraceptive Counseling Measure-scale (PCCC-scale) [65]. Participating women will also receive a follow-up questionnaire six and 12 months after the postpartum visit to evaluate their ongoing contraceptive use and satisfaction with the contraceptive method. In addition, the follow-up questionnaire will ask about unintended or planned pregnancy, induced abortion and miscarriages since the post-partum visit (Table 1).

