### Power analysis and randomisation

The intraclass correlation coefficient (ICC) was set to 0.05 in the power analysis, equivalent to an observed ICC in a similar study [66]. To detect an anticipated 15 percentage point increase in choosing an effective contraceptive method (SARC/LARC) with 90% power at an α = 0.05 (i.e. the probability of rejecting a true null hypothesis), we needed to include at least 30 MHCs, each contributing an average of 100 participants (pregnant women). However, 28 (out of 52) agreed to participate in the study. This implies a statistical power of about 88% which was considered sufficient. The sample size calculations were performed using Stata version 17.0 [67]. No power calculations were performed for secondary outcomes.

The randomisation procedure followed a blocked cluster design. The MHCs (clusters) were first assigned to groups (blocks) based on their regional affiliation and size (number of visits by immigrant mothers in the past year), resulting in two blocks for Jonkoping and Stockholm and three blocks for Vastra Gotaland. Intervention and control status was then randomly assigned to clusters within each block.

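### No clinic-level pre-trial rate of effective contraceptive choice is named for the primary model, so precision may be lost; this is not a bias

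*Protocol article*

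**What the plan says.** In the Protocol article, the section headed cRCT makes the SPR the source of outcome and covariates: "The SPR will be used to retrieve the primary outcome, women’s choice of contraception, and covariates for evaluating social determinants". The examples it gives, and the adjustment set in the Abstract (Methods), are a woman's age, sociodemographic background and reproductive history.

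Statistical analysis describes the primary estimate as obtained "using logistic regression analysis, relying on the randomization scheme to retrieve a causal estimate". Power analysis and randomisation says that clinics were blocked by region and by size, size being the number of visits by immigrant mothers in the previous year. The ICC "was set to 0.05 in the power analysis, equivalent to an observed ICC in a similar study". The aim was a 15-point difference "with 90% power at an α = 0.05", which needed at least 30 clinics averaging 100 women. The section then reports "However, 28 (out of 52) agreed to participate in the study", with power of about 88%.

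On register use, The intervention – a QIC initiative says that midwives in the intervention group will, at each learning session, "analyze and interpret data from the SPR regarding women’s choice of contraceptive methods". Under Eligibility of MHCs and inclusion criteria, clinics in both arms undertake to record contraceptive choice in the SPR; in control clinics this is for consenting women.

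A clinic's earlier rate of effective choice appears neither in the named covariates, nor in the blocking, nor in the power calculation.

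**The concern.** In a trial of 28 clinics, most of the random error comes from clinics that differ before anything is done to them. Covariates measured on women remove that difference only as far as it reflects case mix. Counselling practice and access to methods belong to the clinic. The covariate most likely to capture them is the clinic's own rate in an earlier period, and the outcome comes from a register that is used outside the trial, so that rate may be available cheaply.

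At stake is precision. The trial recruited two clinics fewer than planned. If clinic rates are stable over time, adjustment could more than offset that shortfall and would narrow the confidence interval. It would also correct for a chance imbalance in prior rates, which blocking on region and size need not prevent.

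**Working it through.** **Inputs.** From Power analysis and randomisation: ICC 0.05; m = 100 women per clinic; difference 15 points; α = 0.05; 28 clinics (30 planned). Assumed because not stated: 14 clinics per arm; a two-sided test; control rate 42.5% against 57.5% (the largest variance for a 15-point difference); 100 pre-period women per clinic; and the cluster autocorrelation (CAC), the correlation of a clinic's true rate between the two periods.

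**Step 1: reproduce the stated power.**
- Design effect = 1 + 99 × 0.05 = 5.95.
- Effective women per arm = 1400 / 5.95 = 235.3.
- SE = √[(0.425 × 0.575 + 0.575 × 0.425) / 235.3] = √(0.48875 / 235.3) = 0.0456.
- Noncentrality = 0.15 / 0.0456 = 3.29. Noncentral t with 26 df gives power 0.886.
- With 30 clinics (1500 / 5.95 = 252.1 per arm, 28 df), power is 0.908.

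These agree with the stated figures of about 88% and 90%. Control rates from 35% to 50% give 0.886 to 0.893 at 28 clinics. No baseline adjustment is needed to reach the stated power.

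**Step 2: how much of the error lies between clinics.** Share = 0.05 / (0.05 + 0.95/100) = 0.05 / 0.0595 = 0.84.

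**Step 3: adjust for the clinic's pre-period rate.** The women in the two periods are different, so the correlation of a clinic's observed rates is r = CAC × 0.84. The variance is multiplied by 1 − r², and one degree of freedom is lost (25 df).

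| CAC (assumed) | r | Variance factor | Power, 28 clinics | Difference detectable at about the same power |
|---|---|---|---|---|
| 0 | 0 | 1.000 | 0.885 | 15.0 points |
| 0.3 | 0.252 | 0.936 | 0.905 | 14.5 points |
| 0.5 | 0.420 | 0.823 | 0.936 | 13.6 points |
| 0.7 | 0.588 | 0.654 | 0.974 | 12.1 points |

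The last column is 15 × √(variance factor). Example for CAC 0.5: SE = 0.0456 × √0.823 = 0.0414, and 0.15 / 0.0414 = 3.62.

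**Step 4: sparse registration.** With m₀ pre-period women per clinic, r = CAC × √{[0.05 / (0.05 + 0.95/m₀)] × 0.84}. At CAC 0.5 and m₀ = 30, r = 0.5 × √(0.612 × 0.84) = 0.36 and power is about 0.92, against 0.936 with m₀ = 100.

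**Step 5: block terms.** Reading the article as two blocks each for Jonkoping and Stockholm and three for Vastra Gotaland gives seven blocks. If block terms are fitted and explain nothing, the df are 28 − 7 − 1 = 20 unadjusted and 19 adjusted. Power is then 0.879 unadjusted, and 0.877, 0.897, 0.930 and 0.971 for CAC 0, 0.3, 0.5 and 0.7. The pattern is unchanged.

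**The case against.** The strongest objection is that this is a matter of efficiency in a condensed article. The primary analysis is described in a few sentences, the covariate examples are introduced as examples, the data-collection table is not shown, and a SAP may already specify the adjustment. Clinics are randomised within blocks, so leaving out the baseline rate biases nothing, and the sponsor judged 88% sufficient. All of that stands. It rules out saying that the plan excludes the baseline rate or that the primary analysis is invalid. It does not remove the point: the article does name an adjustment set and blocking factors, and the most relevant clinic-level variable is in neither.

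A reader might also infer from the review of SPR data at every learning session that pre-intervention data must exist. That does not follow. The text covers intervention clinics only and does not say that the data shown at the first session pre-date the intervention. Recording choice is described as an undertaking for the trial, and earlier completeness is not stated for either arm. A covariate available in one arm only cannot be used.

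Two technical objections also stand. Region and size may already explain some of the variation that a baseline rate would explain, which would shrink the gain. The check also works on clinic proportions, whereas the planned model is logistic, where adding a prognostic covariate shifts the conditional odds ratio slightly.

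**Conclusion.** The point holds as a conditional suggestion of low severity. The article names no clinic-level pre-trial rate for the primary model, and with 84% of the variance of a clinic's rate lying between clinics, such a rate could help. A reader might go further and call the gain large; the documents do not support that. The size rests entirely on the CAC, which they do not give. Under the stated assumptions, power runs from 0.885 (a loss of 0.001) at CAC 0 to 0.974 at CAC 0.7, and a CAC of about 0.3 is enough to bring it back to the 90% first aimed for. Nor is the trial shown to be underpowered by its own standard: the 88% reproduces without the adjustment.

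**What to change.** Check first whether SPR contraceptive-choice data of adequate completeness exist for clinics in both arms.

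- **If they do:** extract each clinic's proportion choosing an effective method over a fixed period that ends before randomisation, and prespecify it as a clinic-level covariate in the primary model, alongside the blocking factors. The period should not run up to the first learning session. The randomisation date is not given, the intervention is placed in 2022–2023, and the recording undertakings are worded differently by arm, so a later window could include registrations affected by allocation.
- **If they are incomplete:** keep the primary model as it is and prespecify the adjusted model as a sensitivity analysis.

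The choice should be fixed before outcome data by arm are seen.

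The cost is one register aggregate per clinic and one degree of freedom. The conditional odds ratio shifts slightly with the added covariate, so the report should state what it is conditional on. The gain is smaller where pre-period registration is sparse.
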